## Abstract

**Background:**

Reducing readmissions among frequent users of psychiatric inpatient care could result in substantial cost savings to under-resourced mental health systems. Studies from high-income countries indicate that formal peer support can be an effective intervention for the reduction of readmissions among frequent users. Although in recent years formal peer support programmes have been established in mental health services in a few low- and middle-income countries (LMICs), they have not been rigorously evaluated.

**Methods:**

This protocol describes a quasi-experimental difference-in-differences study conducted as part of a broader evaluation of the Brain Gain II peer support programme based at Butabika National Referral Hospital in Kampala, Uganda. The primary objective is to investigate whether frequent users of psychiatric inpatient care who have access to a peer support worker (PSW+) experience a greater reduction in rehospitalisation rates and number of days spent in hospital compared to those who do not have access to a peer support worker (PSW-). Frequent users, defined as adults diagnosed with either a mental disorder or epilepsy who have had three or more inpatient stays at Butabika over the previous 24 months, are referred to Brain Gain II by hospital staff on five inpatient wards. Frequent users who normally reside in a district where peer support workers currently operate (Kampala, Jinja, Wakiso and Mukono) are eligible for formal peer support and enter the PSW+ group. Participants in the PSW+ group are expected to receive at least one inpatient visit by a trained peer support worker before hospital discharge and three to six additional visits after discharge. Frequent users from other districts enter the PSW- group and receive standard care. Participants’ admissions data are extracted from hospital records at point of referral and six months following referral.

**Discussion:**

To the best of our knowledge, this will be the first quasi-experimental study of formal peer support in a LMIC and the first to assess change in readmissions, an outcome of particular relevance to policy-makers seeking cost-effective alternatives to institutionalised mental health care.

## Background

Frequent users of psychiatric inpatient care, sometimes referred to as “revolving-door”, “high-frequency” or “heavy” users, consume a disproportionate amount of the limited resources available for mental health care [1, 2]. A systematic review of mostly high-income country (HIC) studies estimated 10–30% of users of psychiatric care consume 50–80% of service resources [3].

More recent studies from low- and middle-income countries (LMICs) observe high rates of readmission and large numbers of frequent users among psychiatric inpatient populations [1, 4–9]. In Nigeria, for example, 41.4% of psychiatric inpatients at a university teaching hospital were readmitted within five years. Among those readmitted, mean number of admissions was 2.9 [6]. Meanwhile, the average cost of a single admission to a Nigerian psychiatric hospital is $3675 USD, equivalent to the cost of 90 outpatient visits [10]. Reducing readmissions among frequent users could result in substantial cost savings to under-resourced mental health systems in LMICs.

While there is very little LMIC research investigating service user perspectives on readmission, it is generally acknowledged that readmission can be a profoundly disruptive and demoralising experience [11]. In overstretched psychiatric facilities, experiences of inpatient care may be particularly distressing. Human rights watchdogs have documented overcrowding, unsanitary conditions, abusive practices and other human rights violations at psychiatric inpatient facilities in a number of LMICs [12–16]. According to a survey of people with mental health conditions in LMICs, psychiatric facilities are the fourth worst setting in terms of human rights violations; prisons, by comparison, are sixth [17].

There is evidence from HICs that formal peer support can reduce readmissions [18–21]. Notably, a randomised controlled trial conducted in the United States showed that frequent users receiving formal peer support in addition to standard care had an average of 0.64 fewer readmissions and nine fewer days in hospital than those receiving standard care alone [22]. It is unknown whether similar outcomes can be expected in low-resource settings, as patterns in utilisation of inpatient care can differ substantially from those in high-income countries [23]. There have been no studies to-date on the effectiveness of formal peer support as an intervention to reduce readmissions in a LMIC setting.

Broadly defined, peer support is social emotional support that is mutually offered or provided by “peers”, people with lived experience of mental, neurological or substance use disorders [21, 24]. While peer support encompasses a wide range of different interventions, distinctions are made between formal peer support and informal peer support (or “naturally occurring” peer support, as described by Repper and Carter [2011, pp.393]) [24, 25]. Formal peer support is provided through peer-led programmes or by peers recruited to support roles in traditional mental health or social services [25]. Those offering formal peer support may refer to themselves as “peer support workers” (PSWs) [26], though peer support roles can vary greatly. (For example, the American trial described above employed “peer mentors” to deliver formal peer support [22].) Regardless of their role specifications, PSWs are generally considered to be further along on the road to recovery—able to manage their illness and pursue fulfilling lives—and thus able to leverage their personal experience of recovery to support others [18, 19, 24, 25, 27, 28].

The study described in this protocol is part of a broader evaluation of the Brain Gain II project in Uganda, one of the first LMICs to establish a formal peer support programme [29–31]. The aim of this study is to understand the impact of a formal peer support intervention delivered by trained PSWs on service users’ readmissions. The objective is to investigate whether frequent users of inpatient care who have access to peer support (PSW+) experience a greater reduction in rehospitalisation rates and number of days spent in hospital compared to those who do not have access to peer support (PSW-).

## Methods

As this is not a randomised trial, we first developed our protocol in accordance with STROBE (Strengthening The Reporting of Observational Studies in Epidemiology) guidelines [32], and then checked it against Reeves and Gaus’ (2004) adaptation of the CONSORT (Consolidated Standards of Reporting Trials) checklist for non-randomised studies [33]. Other components of the Theory of Change-driven evaluation have been protocolised and described elsewhere [34, 35]. These include: a cross-sectional survey of recovery-related knowledge, attitudes and practices among Butabika staff; a cost analysis to estimate money saved as a result of reduction in readmissions; a multi-method process evaluation; and additional qualitative methods comprising focus groups and interviews with study participants, PSWs, Butabika staff and other key stakeholders of the Brain Gain II project.

### Setting

Butabika National Referral Hospital (“Butabika”) is a tertiary psychiatric facility with approximately 430 staff and 550 beds [36], though the number of inpatients often exceeds 750 and can approach nearly 1000 [15]. Butabika is located in a largely suburban area of southeastern Kampala, but patients from across Uganda access its services. Standard adult care consists primarily of on-site psychiatric and psychological interventions, and in some cases vocational training, as prescribed by hospital staff. Users in extremely vulnerable situations may be referred to a social worker for additional assistance. After discharge, users typically return to Butabika for outpatient services, attend one of four monthly community outreach clinics (each located within a 20 km radius of the hospital), or access mental health services at district hospitals closer to their homes.

Brain Gain II is a project of the Butabika Link in Uganda—a partnership between Butabika and the East London National Health Service Foundation Trust (ELFT) in the United Kingdom [31]. Brain Gain II aims to reduce the burden on inpatient care at Butabika by promoting recovery among service users on the hospital wards and following discharge. The two main components of Brain Gain II include: (1) establishing an on-campus Recovery College at Butabika, where people with lived and/or professional experience of mental or neurological disorders co-design and co-deliver a recovery-oriented training curriculum; and (2) offering formal peer support by trained PSWs to frequent users of psychiatric inpatient care at Butabika, on five hospital wards and in local communities in four districts [37].

The Butabika Recovery College (BREC) is located in the Community Recovery Team building adjacent to the Forensic Ward. Recovery Colleges are educational (as opposed to clinical) spaces that operate similarly to unaccredited adult education colleges, though with a focus on meaningful involvement of people with lived experience in all aspects of their functioning [38]. At BREC, people with lived experience (mostly PSWs) and people with professional experience (Butabika staff) co-deliver regular teaching sessions on recovery-related topics. Most teaching sessions focus on “what helps” and “what hinders” recovery, identified through a series of Recovery Listening Events held in Uganda by the Sharing Stories Group at the start of Brain Gain II [39]. However, BREC also hosts yoga, bead-making and other skills-based teaching sessions. Most students are current inpatients, though BREC is also open to outpatients, family members and hospital staff.

The Peer Support Office sits within BREC, and acts as the coordinating centre for both Recovery College trainers and PSWs. PSWs operate on five hospital wards, including the forensic ward, acute admissions wards (male and female wards), and long-stay rehabilitation wards (male and female wards). The four districts where PSWs carry out community visits include Kampala, Jinja, Wakiso and Mukono. These are located in the Central and Eastern regions of Uganda and within approximately two hours’ drive of Butabika. Communities in these districts are typically urban or suburban, and English and Luganda are widely spoken.

### Study design

In keeping with Brain Gain II’s emphasis on co-production, it was agreed that both PSWs and staff should be involved in the design and conduct of the project’s evaluation. “A theory of how and why an initiative works” that can be empirically tested (Weiss 1995, p. 86 cited DeSilva et al. 2014, n.page), theory of change is increasingly recognised as a useful tool for involving diverse stakheholder groups in evaluation design [40–42]. Two days of Theory of Change workshops were carried out at Butabika, convening PSWs, Butabika staff and representatives of ELFT. Through guided discussions facilitated by the first author, short-, medium- and long-term outcomes were backward-mapped onto a “pathway of change”, which was further refined in consultation with the project leads at Butabika and ELFT [see Additional file 1]. Indicators were assigned to each outcome and methods proposed to measure each indicator, in order to build up the evaluation design. Methodological decisions were made with a focus on feasibility, understanding that PSWs and staff would be responsible for much of the data collection. As this was funded as a project evaluation, with limited budget for research, there was little scope for hiring external data collectors with the time and specialist expertise required to administer complex measurement tools.

For the evaluation of user-level outcomes of peer support, it was not considered appropriate by stakeholders to adopt an experimental design, in which frequent users in extremely vulnerable situations who could otherwise benefit from peer support in their local communities might not receive PSW visits. Hence, a quasi-experimental difference-in-differences (DID) study design was proposed in which the comparison group consists of those who are referred to the PSW programme but live outside of the four districts that comprise its current catchment area, and therefore do not have access to formal peer support. This design was modelled on a previous evaluation of community-based rehabilitation for people with severe mental disorders in India [43], and compares the change in number of rehospitalisations and hospital days among frequent users who have have access to a PSW (PSW+) to that of frequent users who do not have access to a PSW (PSW-).

### Participants

#### Eligibility criteria

In order to be eligible for inclusion in the study, a service user must: (1) be age 18 years or older; (2) be a Ugandan national currently residing in-country; (3) have been diagnosed with either a mental disorder or epilepsy; (4) have had three or more inpatient stays at Butabika in the previous 24 months; (5) be referred to the peer support programme from one of five participating hospital wards at Butabika; (6) agree to participate in the study (assent) at baseline; and (7) provide either informed consent or guardian consent within the six-month follow-up period (Fig. 1). Although Butabika’s Alcohol and Drug Unit is not one of the hospital wards participating in this study, service users with mental or neurological disorders who also have co-morbid substance use disorders will not be excluded.

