#### Consent

The M&E Officer will assign specialised PSWs called “M&E Buddies” to visit potential participants on the hospital’s wards. M&E Buddies receive enhanced training in research procedures and ethics, including the use of the University of California, San Diego Brief Assessment of Capacity to Consent, a structured tool designed to assist research workers in assessing capacity to consent [44]. During the visit, a M&E Buddy will review the study information sheet and consent form with the participant in either English or Luganda and answer any questions.

All potential participants must assent before baseline data can be collected. Informed consent must also be secured in order for this data to be included in the evaluation. If the M&E Buddy suspects that a potential participant may not have capacity to consent, a guardian can consent as a substitute. Alternatively, a potential participant can provide informed consent at any point over a six-month follow-up period if he or she regains capacity. This provision is made to ensure that potential participants are empowered as much as possible to make their own decisions regarding participation. The process of securing informed consent is illustrated in Fig. 1.

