### Peer support

All participants receive standard adult care and may have some contact with PSWs via the Recovery College. Additionally, participants in the PSW+ group receive face-to-face visits from a trained PSW. Each participant in the PSW+ group is assigned a PSW from a nearby community by an administrator in the Peer Support Office. Peer support visits are offered for up to six months after a PSW is assigned to a user. A recipient of peer support will be visited by a PSW at least once on the ward before discharge, and at least three times after discharge. For particularly vulnerable cases (i.e. three or more inpatient stays in the past 12 months), up to six visits can be made. The PSW visits occur per the recipient’s preference, either at home, at a meeting point in the community, or at the hospital when the recipient returns for outpatient visits. The carer may also be engaged in peer support visits, where possible.

The peer support visits delivered by PSWs are flexible and unstructured, and may consist of any or all of the following:
**Befriending** (social contact, supportive listening and encouragement);**Role-modelling** (sharing personal experiences of illness and recovery);**Psychoeducation** (education on recovery principles);**Problem-solving** (discussing current challenges and possible solutions, liasing with providers to resolve issues with medical and social care as needed).

The qualifications, training, supervision and compensation of PSWs as well as quality assurance for peer support visits are detailed in Table 1.

**Table 1 Tab1:** Brain Gain II Peer Support Workers

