#### Exploratory

Further exploratory analyses will be carried out to help contextualise the results of the main analyses and generate hypotheses for future testing. As primary data collection from the PSW- group is not possible at six-month follow-up, exploratory analyses are limited to the PSW+ group.

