Unfortunately, a randomized control trial was not deemed acceptable for the purposes of this study. Indeed, researchers in HICs have pointed out that randomisation may be in opposition to the principles of self-determination embraced by peer support programmes [71], though some have carried out successful randomised-controlled trials nonetheless. DID is designed to control for time-invariant and group-invariant confounders, but does not entirely eliminate the possibility of confounding or other types of bias. As noted by Wing, Simon and Bello-Gomez (2018): “The DID design is not a perfect substitute for randomized experiments, but it often represents a feasible way to learn about causal relationships” (pp.453).

The study design outlined in this protocol introduces a risk of bias, as the two study groups differ by district of residence. There is a possibility that unmeasured time- and group-variant factors may differ between districts and confound the relationship between peer support and use of inpatient care. Peer support is only available in four districts of the relatively prosperous Central and Eastern regions near the country’s capital city, Kampala, where Butabika is located. Further, this is not a blinded study, though PSWs responsible for delivering the intervention do not collect study data from their assigned peers, and neither PSWs, M&E Buddies nor the Peer Support Office Administrator have access to admissions data.

In addition, the outcomes compared between groups are limited to those which can be assessed using the hospital’s routinely collected data. Loss-to-follow-up after discharge from inpatient care is a significant issue for Butabika, which PSWs help to remedy through regular visits to the community. The comparison group does not have contact with PSWs after discharge. Therefore, stakeholders deemed it unfeasible to collect primary data from a significant number of participants in the comparison group. The Indian evaluation upon which this study is based faced similar challenges; outcomes could not be assessed in about a third of all participants in the comparison group [43].

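### Consent may be given at any time in the outcome window, and PSW- users who leave the index stay without it are more likely to be reached if readmitted, so inclusion can depend on the outcome differently by group

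*Protocol article*

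**What the plan says.** All places are in the protocol article.

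- **Consent is a condition of inclusion.** Criterion 7 under Eligibility criteria requires users to "provide either informed consent or guardian consent within the six-month follow-up period". The Consent section adds: "Informed consent must also be secured in order for this data to be included in the evaluation".
- **Late consent is allowed.** The same section opens a later route for the user's own decision: "a potential participant can provide informed consent at any point over a six-month follow-up period if he or she regains capacity". The stated aim is to let users make their own decision wherever they can. The other route, where capacity is in doubt, is that "a guardian can consent as a substitute".
- **Where consent is sought.** M&E Buddies are assigned "to visit potential participants on the hospital’s wards".
- **Contact after discharge, PSW+.** Under Peer support, recipients are to be visited "at least once on the ward before discharge, and at least three times after discharge". The Exploratory section has M&E Buddies collecting questionnaire data from this group at six months.
- **Contact after discharge, PSW-.** The Discussion says: "The comparison group does not have contact with PSWs after discharge". The Exploratory section says that "primary data collection from the PSW- group is not possible at six-month follow-up".
- **Outcome window.** Hospital days and rehospitalisations are counted from records over the six months after referral, with the index stay excluded (Outcomes).

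The Missing data section expects low attrition because the main analyses need no follow-up contact. It does not consider consent obtained after discharge. Neither Bias nor the Discussion mentions selection through late consent.

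**The concern.** Entry to the analysis can be decided by something that happens while the outcome is being counted. That does little harm if late consent is unrelated to readmission, or related to it in the same way in both groups. Here the chance of meeting a consent-taker again differs by group. PSW+ users have a planned M&E Buddy contact at six months whether or not they were readmitted. For PSW- users the only consent setting described is the ward, and being back on a ward is the outcome.

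PSW- users who stay out of hospital would then be dropped more often than those who return. Follow-up use in the comparison group would be too high, and the group-by-time interaction would show a benefit of peer support even with no true effect. Difference-in-differences does not remove this, because the selection acts on follow-up use. If the timing of consent is not recorded, the distortion cannot later be separated from a real effect.

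**Working it through.** The plan gives no figure for this point, so there is none to reproduce. The calculation shows how large the bias could be.

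**Inputs**
- u: share of PSW- users without own or guardian consent at index discharge who can be reached only through readmission. Not stated; assumed 5% to 30%.
- m: mean stays in six months. Not stated; assumed 0.5 to 1.0. The centre comes from the entry threshold of three stays in 24 months: 3 × 6/24 = 0.75.
- No true effect. Every readmitted PSW- user in the affected subset consents, and late consent in PSW+ does not depend on outcome.

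**Step 1: follow-up mean in PSW-.** The excluded users have no stays. If P0 is the probability of no readmission, then

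mean among those included = m / (1 − u·P0).

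**Step 2: stays independent between baseline and follow-up (Poisson).** P0 = exp(−m), and the baseline mean is unaffected. Bias as a share of m = u·P0 / (1 − u·P0).

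At m = 0.75, P0 = 0.472:
- u = 10%: 0.75/(1 − 0.0472) = 0.787, bias 5.0%
- u = 20%: 0.75/(1 − 0.0945) = 0.828, bias 10.4%
- u = 30%: 0.75/(1 − 0.1417) = 0.874, bias 16.5%

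**Step 3: correlated use.** Users differ in their underlying rate, so those selected for readmission also have higher baseline use, and the difference-in-differences subtracts part of the bias. With a gamma-distributed rate (shape 1) and Poisson counts, P0 = 1/(1 + m) and the contribution of non-readmitted users to baseline stays is m/(1 + m)². The bias as a share of m is then

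[u/(1 + m)²] / [1 − u/(1 + m)].

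At m = 0.75 and u = 20%: (0.2/3.0625)/(1 − 0.2/1.75) = 0.0653/0.8857 = 7.4%. Follow-up rises to 0.847 and baseline to 0.792.

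**Results: bias in favour of PSW+, as % of the mean**

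| m | u | Independent | Correlated |
|---|---|---|---|
| 0.5 | 5% | 3.1 | 2.3 |
| 0.5 | 20% | 13.8 | 10.3 |
| 0.5 | 30% | 22.2 | 16.7 |
| 0.75 | 5% | 2.4 | 1.7 |
| 0.75 | 20% | 10.4 | 7.4 |
| 0.75 | 30% | 16.5 | 11.8 |
| 1.0 | 5% | 1.9 | 1.3 |
| 1.0 | 20% | 7.9 | 5.6 |
| 1.0 | 30% | 12.4 | 8.8 |

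A simulation of two million users per setting agrees with these formulas to within 0.1 percentage point. The formula in step 1 also holds for hospital days, since the excluded users have none. With consent fixed before discharge in both groups, u = 0 and this bias is 0.

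**The case against.** A reader might infer that uncapacitated PSW- users can enter **only** if readmitted. The article does not say that. Guardian consent is open equally to both groups, and capacity may return before index discharge, particularly on the long-stay wards. The Setting section also says that discharged users commonly come back to Butabika as outpatients. The Discussion rules out contact with PSWs, not all contact, and it calls primary data collection unfeasible for a significant number of PSW- users rather than for every one. Only users missed by all these routes are affected, and their number is unknown. This stands, and it is why u is defined narrowly above.

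A reader might also infer that PSW home visits secure late consent in PSW+ whatever the outcome. Home visits are not a stated consent route: M&E Buddies take consent, and a participant's Buddy may not be his or her PSW. The asymmetry rests on the six-month Buddy contact. If late consent in PSW+ is incomplete and also favours readmitted users, part of the bias cancels.

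Nor would baseline use stay unchanged among those selected. It would rise somewhat, and step 3 allows for that. Readmitted users may again lack capacity, which would weaken the selection further.

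Finally, the consent flow chart and the further ethical procedures are not in the text at hand and may describe how PSW- users are re-approached. That could shrink u. It would not change criterion 7, which lets inclusion be settled inside the outcome window.

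**Conclusion.** The point holds in limited form. Inclusion can depend on readmission, and more so in PSW- than in PSW+, with a bias towards peer support under the assumptions above. Its size cannot be determined from the article. Over the assumed ranges it runs from about 1% to 22% of the mean, or about 1% to 17% with correlated use. At u near 5% it is small (1.3% to 3.1%); at u = 20% it is material (5.6% to 13.8%).

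A reader might set these percentages directly against the 20% effect in Study size. The article ties that figure to Cohen, so it may be a standardised effect, and the supporting file is not shown; the units may not match. Nor do the documents show that the results will be distorted to any given degree. The case for acting is that the direction is predictable, the design does not correct it, and the remedy costs little.

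**What to change.** 1. Define the primary analysis set, identically in both groups, as users with own or guardian consent recorded before discharge from the index stay.
2. Keep the late-consent route for its stated ethical purpose, but add those users only in a sensitivity analysis.
3. Record the date and route of consent (own or guardian; index stay, later ward stay, outpatient visit or six-month contact). Report by group how many referred users consented at each stage and how many never did.

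This is a change of analysis-set wording plus two data items. The cost is a slightly smaller primary set that under-represents users without capacity or a guardian. That limit on generalisability should be stated, and the sensitivity analysis would show how far the result moves when late consenters are added.
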